## Abstract

**Objective:** Exercise rehabilitation is an effective therapy in reducing the disability rate after stroke and should be carried out as early as possible. However, very early rehabilitation exercise exacerbates brain injury and is difficult to conduct in stroke patients due to their weakened and potentially disabled state. It is valuable to explore additional early rehabilitation strategies. Remote Ischemic Conditioning (RIC) is a novel therapy designed to protect vital organs from severe lethal ischemic injury by transient sublethal blood flow to non-vital organs, including the distal limbs, in order to induce endogenous protection. RIC has previously been conducted post-stroke for neuroprotection. However, whether combined early RIC and exercise (RICE) therapy enhances stroke rehabilitation remains to be determined.

**Methods:** This is a single-center, double-blinded, randomized controlled trial that will enroll acute ischemic stroke patients within 24 h of symptom onset or symptom exacerbation. All enrolled patients will be randomly assigned to either the RICE group (exercise with RIC) or the control group (exercise with sham RIC) at a ratio of 1:1, with 20 patients in each group. Both groups will receive RIC or sham RIC within 24 h after stroke onset or symptom exacerbation, once a day, for 14 days. All patients will begin exercise training on the fourth day, twice a day, for 11 days. Their neurological function [Modified Rankin Scale (mRS) score, National Institutes of Health Stroke Scale (NIHSS) score, Barthel Index, and walking ability], infarct volume (nuclear magnetic resonance, MRI), and adverse events will be evaluated at different time points in their post-stroke care.

**Results:** The primary outcome is safety, measured by the incidence of any serious RICE-related adverse events and decreased adverse events during hospitalization. The secondary outcome is a favorable prognosis within 90 days (mRS score < 2), determined by improvements in the mRS score, NIHSS score, Barthel Index, walking ability after 90 days, and infarct volume after 12 ± 2 days.

**Conclusion:** This study is a prospective randomized controlled trial to determine the rehabilitative effect of early RIC followed by exercise on patients with acute ischemic stroke.

**Trial Registration:**
www.chictr.org.cn, identifier: ChiCTR2000041042

## Introduction

Stroke is a leading cause of death and disability worldwide (1, 2), with an annual mortality rate of approximately 5.5 million (3). Through the application of evidence-based control measures, the burden of stroke death has declined in many developed countries—in the Western world, death from stroke declined by 30–50% from 1975 to 2005 (4). However, despite an increase in the rate of effective life-saving interventions, such as vascular recanalization by intravenous thrombolysis and intravascular therapy, over 50% of the survivors are left with new disabilities (5). Therefore, stroke remains as a disease of enormous public health importance, and the need for an effective stroke rehabilitation beyond mortality reduction is growing as an essential part of the continuum of stroke care. Acute ischemic stroke, in which an embolic or thrombotic event occludes an artery supplying the brain, accounts for 80% of all strokes (4) and thus represents an unmatched source of devastating disability (6).

Stroke protocols are carried out within hours of the cerebrovascular accident in order to maximize penumbral reperfusion and tissue recovery (7–9). Analogously, rehabilitation techniques, which can also enhance reperfusion and are an indispensable component of promoting the functional recovery of stroke patients, should be carried out as early as possible. Numerous clinical studies have demonstrated that exercise enhances motor function after a cerebrovascular accident (10). Therefore, national guidelines for improving stroke outcomes recommend early exercise rehabilitation (11). However, A Very Early Rehabilitation Trial (AVERT) demonstrated that very early mobilization (<24 h) after stroke actually exacerbated brain injury and reduced rates of favorable prognoses measured at 3 months (12, 13). Similar results were also found in our clinical study (14). Furthermore, patients at the early stages of recovery from stroke had unstable body conditions and poor endurance and found it difficult to adapt to exercise training, which limited the promotion of early exercise rehabilitation after stroke (15). Moreover, since patients differ in the nature of their cerebrovascular accidents and resulting disabilities; it is difficult to recommend and implement standardized rehabilitation protocols that are both safe and effective for all stroke patients. These findings point to a gap in the continuum of stroke care at its early recovery stages: theoretically, early exercise intervention is beneficial to stroke victims, but the practicality of exercise rehabilitation limits its clinical applications. This gap calls for exploration of different novel, simple, and feasible rehabilitation models to be implemented in the early stages of recovery—when exercise poses greater harm than good.

Remote ischemic conditioning (RIC) is a novel therapy that was initially developed in the realm of cardioprotection after myocardial infarction, where it was shown to reduce infarct size, minimize ischemia/reperfusion injury, and prevent the onset of heart failure (16). More recently, it has emerged for victims of cerebrovascular accidents due to its non-invasive, easy-to-administer, and low-cost nature (17). RIC involves the induction of transient sublethal ischemia *via* controlled blood flow restriction to the distal limbs, which induces endogenous protective effects against severe lethal ischemic injury to vital organs of the body, such as the heart, brain, and kidney (18). RIC has been shown to function by similar biochemical mechanisms as physical exercise, such as through the promotion of neurogenesis and angiogenesis, which are essential for post-stroke rehabilitation (19, 20).

Studies have demonstrated RIC to be an effective prophylactic therapy for acute ischemic stroke in patients with symptomatic intracranial arterial stenosis (SIAS) (21) and during carotid artery stent placements (22). In post-stroke therapy, RIC has been shown to enhance cognitive function, particularly in the domains linked to visuospatial, executive functioning, and attention (23). Furthermore, long-term application of RIC appears to have the same benefits to the human body as exercise (24) and has been shown to improve walking speed and to reduce neuromuscular fatigue in chronic stroke survivors (25). These studies and others suggest that the use of RIC in stroke patients enables a similar spectrum of benefits as exercise therapy without many of its associated drawbacks. In contrast to physical activity, RIC is administered to the patient passively and depends less on his or her motivation, level of physical activity, and degree of post-stroke disability, especially at the early stage. Indeed, RIC is performed through the basic application of a blood pressure cuff to the arm for sessions measured in minutes, and is thus feasible for patients irrespective of their clinical picture (26). However, research on RIC is in its infancy, and it is still unclear whether it can be used as a unique component, or eventually as the sole therapy, of early rehabilitation to improve neurological function after stroke.

In this study, we will evaluate the safety and feasibility of RIC with exercise (RICE) as a novel rehabilitation strategy in patients with acute ischemic stroke. RIC, a simple procedure, will be implemented as early as possible to initiate rehabilitation closer to the onset of the ischemic event and into the time frame in which early exercise rehabilitation was shown to exacerbate brain injury. It will be combined with exercise, implemented at the time at which it has been shown to promote functional recovery and improve long-term functional prognosis. Clinical improvement with very early RIC would highlight RIC as an effective rehabilitation method that could bridge the gap in the continuum of very early post-stroke care. Marked improvement in the dual therapy group could also point to an additive or synergistic effect of exercise and RIC therapy, namely, the RICE.

## Methods

### Study Design

This is a single-center, double-blinded, randomized controlled trial that will enroll acute ischemic stroke patients within 24 h of the ischemic event or symptom exacerbation. All participants will be informed about the clinical study and the requirement to give informed consent. The study protocol and informed consent were approved by the regional ethics committee and have been registered with the Clinicaltrials.gov (ChiCTR2000041042).

After receiving informed consent, all enrolled patients will be randomly assigned to either the intervention group (RIC with exercise rehabilitation) or the control group (sham RIC with exercise rehabilitation) at a ratio of 1:1, with 20 patients in each group. Within 24 h of the ischemic event or symptom exacerbation, the groups will start either RIC or sham RIC in 45-min sessions, once a day, for 14 days. All patients will begin exercise rehabilitation training 4 days after the ischemic stroke event in 30-min sessions, twice a day, for 11 days. Brain imaging with MRI will be performed on the day of the stroke for a baseline and again at 12 days. Evidence of stroke severity and disability will be evaluated using the National Institutes of Health Stroke Scale (NIHSS) score and the Barthel Index, which will be administered by trained investigators blinded to the treatment assignment on the day of the stroke for a baseline and at 1, 3, 7, and 90 days after enrollment. Furthermore, the Modified Rankin Scale (mRS) will be administered, and walking ability will be assessed at 90 days.

### Patient Population

Participants will be recruited from the hospital wards. The inclusion criteria for recruitment are as follows: (1) age: 18–80 years old; (2) patients with confirmed acute ischemic stroke (mRS ≤ 2 and NIHSS score: 6–16), including those who received intravenous thrombolysis or mechanical embolectomy; (3) randomized grouping ≤24 h of stroke onset or symptom exacerbation; and (4) written informed consent provided by the participant or legally authorized representative. The exclusion criteria for recruitment include the following: (1) contraindications for ischemic conditioning (e.g., severe soft tissue injury, fracture, and peripheral vascular disease in both upper limbs); (2) unstable vital signs (e.g., systolic blood pressure <120 or >220 mmHg, heart rate <40 beats/min or >100 beats/min, percutaneous oxygen saturation ≤92%, body temperature ≥38.5°C); (3) lower limb fracture(s) or other factors that would prevent exercise training completion; (4) history of poor compliance; (5) life expectancy ≤1 year; (6) severe hepatic, pulmonary, and/or renal dysfunction; (7) coagulation dysfunction or active bleeding; (8) combined acute coronary syndrome or severe arrhythmia; (9) pregnant or lactating patients; and/or (10) participation in another clinical trial currently or within 30 days before study inclusion.

### Randomization

All enrolled patients will be randomly assigned to either the intervention group or the control group at a ratio of 1:1. Randomized sequence column orders will be made according to a predefined table generated by a computer program. The random sequence will be hidden in an enclosed opaque envelope. After the baseline patient data are collected by a specialized member of the research personnel, subjects will be randomly assigned to either the intervention group or the control group.

### Interventions

RIC will be performed by placing an electronic tourniquet around both arms within 24 h of stroke symptom onset or symptom exacerbation. Participants in the intervention group will undergo five cycles of cuff inflation to 200 mmHg for 5 min, followed by deflation for 5 min. This will be repeated once daily for the subsequent 14 days. Patients in the sham RIC group will receive the same procedure as the treatment group, but the maximal inflation pressure will be set to only 60 mmHg.

All patients will receive daily out-of-bed exercise training twice a day for 30 min, starting from 4 days after symptom onset, for 11 days. Out-of-bed mobilization, as described previously by us (14), will include sitting, standing, and walking, which will be performed with or without assistance. While no special equipment will be used, mobilization will permit the use of standing bed and wheelchair when necessary. All mobilization protocols will be adjusted to each individual patient's tolerance, needs, and abilities and will be delivered by professional therapists or nurses. The frequency, dose, and content of mobilization will vary according to the individual patient's physical ability and will be recorded in detail by therapists or nurses. The dose of exercise will be monitored by a specially assigned staff to ensure good compliance for this study. Physicians will be asked to evaluate patients with deteriorating conditions during the exercise and to postpone mobilization when necessary (14). Patients in both groups will receive standard stroke treatment according to the guidelines, including thrombolysis, anti-platelet aggregation, and lipid reduction (Figure 1).

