RIC is a non-invasive, feasible, and promising rehabilitative method for patients recovering from ischemic stroke. It has been demonstrated that post-stroke RIC training can be carried out safely within 6–24 h of acute ischemic stroke attack and induce a significant neuroprotective and neurorehabilitative effect (39). Hence, RIC training will be initiated within 24 h after stroke onset in this study.

Very early exercise rehabilitation with physical exercise after stroke may aggravate brain injury and reduce the rate of good prognosis at 3 months post-cerebrovascular event (47). Previous expert consensus also recommends that exercise rehabilitation treatment be conducted within 48–72 h after stroke, after which patients have regained stable vital signs and no longer have acutely deteriorating neurological symptoms (12). Therefore, in this study, out-of-bed exercise rehabilitation will be carried out 72 h after stroke attack, that is, on the fourth day of stroke. Early RIC combined with follow-up exercise training is a novel early rehabilitation model for acute stroke patients; therefore, we set the duration of RIC and exercise rehabilitation to be 14 days according to the protocol of “A Very Early Rehabilitation Trial” (AVERT) (48), the most well-known and evidence-based clinical study on early rehabilitation of stroke.

In this way, our study will employ two treatments that are known to be effective in stroke rehabilitation at their respective temporal windows that are known to maximize benefits and reduce adverse events. This temporal optimization will enable stroke patients to benefit from the individual advantage of RIC and exercise rehabilitation and perhaps from a temporal and synergistic role of the two therapies.

There are some limitations to this study. First, as previous research is lacking, the sample size was calculated based on previous relevant literature (27, 28). Additionally, the patient population is highly targeted in this study: we have limited the inclusion criteria to patients with moderate acute cerebral infarction and moderate-to-high disability rate (NIHSS scores 6–16). Therefore, the results may not be accurately generalizable to all patients with acute cerebral infarction. Future directions should seek to apply this modem of post-stroke therapy to patients with infarcts varying in size and severity as well as diverse degrees of post-stroke disability as determined by the NIHSS score.

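### The upper systolic limit for entry (220 mmHg) lies above the fixed active cuff pressure (200 mmHg), so in patients at 200–220 mmHg the RIC dose may be partial (minor).

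*Protocol article*

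**What the plan says.** Protocol article, Patient Population, exclusion criterion 2: unstable vital signs exclude a patient, and the examples include "systolic blood pressure <120 or >220 mmHg". This is the only upper systolic limit in the article.

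Interventions: active patients receive "five cycles of cuff inflation to 200 mmHg for 5 min, followed by deflation for 5 min" on both upper limbs. The sham procedure is the same, except that "the maximal inflation pressure will be set to only 60 mmHg". The cuff pressure is one fixed number and is not tied to the patient's own pressure.

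Introduction, on mechanism: "RIC involves the induction of transient sublethal ischemia", brought about by "controlled blood flow restriction to the distal limbs, which induces endogenous protective effects against severe lethal ischemic injury".

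On timing, Study Design gives "either RIC or sham RIC in 45-min sessions, once a day, for 14 days", and the Discussion adds that "RIC training will be initiated within 24 h after stroke onset in this study". Randomisation must also fall within 24 h of onset or symptom exacerbation (inclusion criterion 3).

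**The concern.** The entry limit and the cuff pressure are both stated, and they do not fit together. A cuff inflated to a pressure at or below systolic pressure cannot be relied on to make the limb ischaemic. The criteria nevertheless admit patients for whom the single active setting is in that position.

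The first session is the most exposed. Randomisation and session 1 share the same 24 h window, so the pressure accepted at entry can be close to the pressure at treatment.

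RIC is the only component that differs between the groups, since everyone receives exercise and standard care. What is at stake is whether the active group receives the full intended dose in every session. This bears on the between-group contrast in the secondary efficacy outcomes, and slightly on how far the safety data describe the intended dose.

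**Working it through.** The article has no figure of its own to reproduce here. The check compares the stated pressures and then asks how much treatment could be affected.

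**Inputs from the article.** Active cuff 200 mmHg and sham cuff 60 mmHg (Interventions); eligible systolic range 120–220 mmHg (Patient Population); 20 patients per group and 14 daily sessions (Study Design).

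**Step 1: margin = cuff pressure − systolic pressure.**

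| Systolic (mmHg) | Active margin (mmHg) | Active cuff / systolic | Sham cuff / systolic |
|---|---|---|---|
| 180 | +20 | 111% | 33% |
| 199 | +1 | 101% | 30% |
| 200 | 0 | 100% | 30% |
| 220 | −20 | 91% | 27% |

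Across 200–220 mmHg the active cuff is level with systolic pressure or up to 20 mmHg below it. Even at 220 mmHg it is 140 mmHg above the sham setting, so the two procedures remain far apart.

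**Step 2: what one affected patient means in sessions.** The active group has 20 × 14 = 280 sessions.

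- One affected session: 1/280 = 0.36%.
- One patient affected for 3 sessions: 3/280 = 1.1%.
- One patient affected for all 14: 14/280 = 5.0%. This needs systolic pressure to stay at 200 mmHg or more for two weeks, which nothing in the article suggests.

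**Step 3: how many patients (illustration only).** The article gives no blood-pressure distribution. Assume systolic pressure is normal and truncated to the eligible range. The share at 200–220 mmHg is p = [F(220) − F(200)] / [F(220) − F(120)], where F is the normal distribution function.

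| Assumed mean / SD | p | Expected patients, 20p | P(none), (1 − p)^20 | P(3 or more) |
|---|---|---|---|---|
| 145 / 20 | 0.3% | 0.06 | 94% | <0.1% |
| 155 / 25 | 3.4% | 0.68 | 50% | 2.9% |
| 165 / 25 | 7.0% | 1.41 | 23% | 16% |

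P(3 or more) is binomial with n = 20.

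**Step 4: expected share of active sessions affected = p × k/14**, where k is the number of affected sessions per affected patient.

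- k = 1: 0.02% to 0.50%.
- k = 3: 0.07% to 1.5%.
- k = 14: 0.32% to 7.0%, the unlikely extreme.

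**Step 5: the price of a lower entry limit under the same assumptions.** Excluding at ≥200 mmHg removes the share p, 0.3% to 7.0% of otherwise eligible patients. Excluding at >180 mmHg removes [F(220) − F(180)] / [F(220) − F(120)]:

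- 145 / 20: (0.9999 − 0.9599)/(0.9999 − 0.1056) = 4.5%.
- 155 / 25: (0.9953 − 0.8413)/(0.9953 − 0.0808) = 16.8%.
- 165 / 25: (0.9861 − 0.7257)/(0.9861 − 0.0359) = 27.4%.

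**The case against.** The strongest case against the point is that it has almost no consequence. No blood-pressure data are given, so every patient count above is assumed, and even the assumed ranges leave a 23% to 94% chance that no active patient is affected. The trial is described as phase 1 for safety and feasibility, efficacy is secondary, and the sample size does not rest on a power calculation. All of this stands, and it is why the point is minor.

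Second, the Introduction speaks of restricting blood flow, not of complete arterial occlusion. This also stands. The article does not say that RIC fails unless inflow stops entirely, so the most that can be said is that ischaemia is not assured.

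Third, the vital-sign limits are given as examples and describe entry, not an operating range for the device. A pressure check before each session may well be in the full protocol, and its absence from a journal article is no finding. That narrows the point to the two stated numbers but does not reconcile them. No stricter upper limit appears anywhere, and a session rule elsewhere would leave the published entry limit above the published cuff pressure.

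A reader might go further and infer that sessions at 200–220 mmHg amount to sham, that a material part of the active group is under-dosed, or that the safety result is compromised. The article supports none of these. The cuff stays far above the sham setting, the 5% and 7% session shares need 14 days of sustained very high pressure, and every such patient remains in the safety analysis.

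**Conclusion.** The mismatch is real and can be read directly from two stated numbers: the criteria admit patients up to 220 mmHg, and the active cuff is fixed at 200 mmHg. In a session at 200–220 mmHg the active dose may be partial.

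The size is small. Probably few of the 20 active patients, and possibly none, are affected. With one to three affected sessions per such patient, the expected share of active sessions is 0.02% to 1.5%. These figures rest on assumed truncated normal distributions and not on trial data. The certainty attaches to the mismatch, not to any effect on results. The effect on the primary safety outcome is negligible. Severity: minor.

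**What to change.** **Entry.** Lower the upper systolic limit in exclusion criterion 2. A limit of ≥200 mmHg is the least that puts the cuff above systolic pressure at entry, but a patient at 199 mmHg then has a margin of only 1 mmHg. A limit of >180 mmHg gives at least 20 mmHg and is the better choice if recruitment allows.

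**Sessions.** Add to Interventions, for both groups so that the sham procedure stays matched: measure systolic pressure before each session; if it is at or above the limit, re-measure and postpone within the same day. Session 1 must not be postponed past the 24 h window. Any session delivered above the limit is given as scheduled and recorded as a partial dose, with the reading.

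**Cost.** One changed number and two or three sentences. Under the assumed distributions, ≥200 mmHg excludes about 0.3% to 7% of otherwise eligible patients and >180 mmHg about 4.5% to 27%. The stricter limit could therefore slow a 40-patient single-centre trial noticeably. The site's own admission pressures should decide between them. Some sessions will start later in the day.

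Setting the cuff above each patient's own pressure would avoid the exclusions. It would need more than 220 mmHg at the top of the present range, and it would replace the single fixed dose whose safety the trial is meant to describe.
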